### Assessment instruments

#### Behavioral checklist for children with high-functioning autism/Asperger’s disorder high-functioning autism checklist

The Behavioral Checklist for Children with High-Functioning Autism, developed by Jung-Fen Chang, will be utilized in this study. This scale consists of two parts: the first is a primary survey, while the second is a 60-question quiz for reference purposes. The questions are categorized into three groups- social, communication, and behavioral - to evaluate Asperger’s disorder in these domains (37).

#### Autism behavior checklist

The ABC was initially established by Krug et al. in the United States in 1978 and subsequently validated in 1980 to determine its psychometric properties, demonstrating a reliability coefficient of 0.87 (38). The checklist comprises 57 elements categorized into five groups: sensory, relational, body and object usage, language, and socialization/self-help. Scores are based on a four-point frequency scale, with higher scores indicating more abnormal behavior. Each sub-scale’s total score can be calculated by calculating the domain fractions and overall fractions. These scores provide an indication of the severity of the behavioral characteristics associated with autism, with higher scores reflecting more prominent features (38). It is commonly implemented for screening individuals aged 3-35. ABC Scale has gained popularity as a screening tool for autism spectrum disorder due to its user-friendly nature, ease of scoring, and cost-effectiveness.

#### CABS

The CABS is a parent-reported autism diagnostic scale compiled by Clancy in 1969 comprising 14 entries. Tse Ching Fen et al. revised the scale in Taiwan in 1983, replacing the original 2-point method with three types of reaction strength: “never 0,” “occasionally 1-point,” and “often 2-point”. A total score of ≥14 serves as the preliminary screening criteria for autism, while a total score of ≥14 points combined with a “never” item score of <3. Moreover, a “regular” item score of ≥6 can be used to diagnose autism (39). The CABS scale is presently regarded as the most extensively utilized autism screening tool in Mainland China.

#### Social responsiveness scale

Children with autism aged 4-18 are routinely tested by the SRS. Social contact, social cognition, social interest, social motivation, and daily routines are among the 65 items in the SRS that describe children’s daily social experiences. Studies have examined the use of the SRS for screening autism spectrum disorders in children over four years of age. In 2017, Cen et al. evaluated the use of the SRS scale in China (40). The study found that the scale demonstrated excellent reliability and validity, supporting its usage in clinical and related research. Li et al. assessed the reliability and validity of the SRS scale in 275 children in 2018. The results indicated 59.8% sensitivity, 77.5% specificity, and 88.4% positive predictive value (41).

#### Wechsler intelligence scale

The Wechsler Intelligence Scale for Children’s Chinese version will be used to assess the participants’ intelligence (26). The test follows a national norm in urban and rural editions. Test-retest reliability of 0.59 to 0.86 is shown by a split-half correlation coefficient of 0.8 and an IQ split-half reliability of 0.9 (42). Additionally, the scale has been validated structurally. This tool is widely recognized as an essential measure of children’s IQ levels in China.

### Interventions

Inclusion of patients with HFA will be randomized into one of two groups. For the active group, patients will be subjected to a 25 Hz stimulation frequency, 250 s pulse width, and a 30-s on/30-s off cycle for a total of 2 hours divided into four 30-minute periods. Patients remain quiet during each 30-minute session. The stimulation intensity will be adjusted to a level where patients experience the maximum tolerable intensity of pain (43–45). In contrast, the sham group will undergo a placebo procedure designed to mimic the active treatment condition. The sham group will be positioned anatomically identical to the active treatment group, receiving the same duration of treatment. However, the stimulation frequency will be set at 1 Hz, and the intensity level will only elicit the minimum perceptible tingling sensation, creating the illusion of active stimulation. The National Institutes for Food and Drug Control (NIFDC)-certified taVNS device TVNS-100 (Xinzhile, Jiangxi, China) will be utilized for the taVNS procedure, with electrodes placed on both the inner and outer surfaces of the tragus in bilateral ears (43). Patients and caregivers will receive professional instructions on how to operate the stimulator and then perform the stimulation by themselves routinely. In addition, patients and caregivers will be instructed to promptly monitor and report any potential side effects, such as headache, tinnitus, vertigo, or nausea, to their doctors during or after stimulation. Depending on the situation, the stimulation intensity may be adjusted, or the stimulation may be stopped.

### MRI scanning

#### MRI sequences

The MR750 3.0T MRI scanner (GE Healthcare, USA) will be utilized to scan all participants at Beijing Children’s Hospital’s Department of Radiology. A three-dimensional (3D) magnetization-prepared rapid gradient echo sequence with the following parameters will be used to obtain T1-weighted images: repetition time (TR)/echo time (TE)/inversion time (TI)=2530/2.34/1100 ms, flip angle = 7°, slice count = 176, section thickness = 1mm, matrix size = 256×256. The duration of the T1 sequence was 649 seconds. Subsequently, T2-weighted image scans lasting for 60 seconds will be performed on all participants to eliminate the possibility of incidental disorders of the central nervous system (46).

Functional image data (Resting-state fMRI, rs-fMRI)will be obtained using T2-weighted echo planar imaging with the following parameters: TR/TE =2500/21 ms, flip angle=90°, number of slices=42, slice thickness=3.5 mm, field of view (FOV)=20×20 cm^2^, matrix size =64×64, voxel size=3.1×3.1×3.5 mm^3^, and bandwidth=2.52 kHz/Px. An echo planar imaging sequence will be used to acquire the diffusion data, with parameters TR/TE =7000/70 ms, flip angle=90°, data matrix size =112×112, FOV= 20×20 cm^2^, slice thickness=2 mm, number of slices=60, and scanning time= 9 minutes and 40 seconds. For the 3D T1-weighted turbo field echo sequence and parameters will have the following parameters: TR/TE=12/5.9 ms, flip angle=8°, matrix size=256×256, FOV =25.6×25.6 cm^2^, slice thickness=1.6 mm with 0.8 mm gaps between slices, number of slices=180, and scanning time= 5 minutes and 56 seconds. All participants will be given clear instructions to keep their eyes closed during the scanning procedure while ensuring they remain awake.

#### MR preprocessing

Each participant’s rs-fMRI data will be preprocessed using Statistical Parametric Mapping software (SPM12) and a powerful toolbox called Data Processing & Analysis of Brain Imaging (DPABIV7.0). The following specific steps will be performed for each subject: converting the DICOM to NIFTI format, removing the first ten time points to exclude the effects of subject maladaptation and magnetic field inhomogeneity at the beginning of the scan, and leaving the remaining time points for further spatial and temporal alignment and head rotation correction. If the subject’s head movement is >2 mm in the translation range or >2 ° in rotation, the subject’s data should be excluded. Additionally, time and spatial normalization procedures will be conducted. The images will be aligned to the Montreal Neurological Institute (MNI) space, with each voxel measuring 3 × 3 × 3 mm³. Nuisance covariates, including the Friston 24 parameter model, as well as signals from cerebrospinal fluid and white matter, will be removed through regression analysis to correct the realigned data. A 4 mm full width at half-maximum isotropic Gaussian kernel was utilized for spatial smoothing, while linear signals were eliminated. Furthermore, a temporal band-pass filter will be applied, restricting the frequency range to 0.01–0.08 Hz (47). The diffusion tensor imaging data preprocessing will be conducted using the open-source software Pipeline for analyzing brain diffusion images (PANDA), which also allows for the construction of brain networks and can be downloaded at http://www.nitrc.org/projects/panda/. The preprocessing typically involves several key steps. First, the 3D T1 structural image will be co-registered with the b0 image to eliminate the effects of eddy current distortions and motion artifact; next, extraction of brain tissue from corrected data, removal of scalp and other non-brain tissue structures; the diffusion space will be subsequently aligned with the T1 template, utilizing the MNI space as a reference. Thus, the diffusion space will be mapped to the MNI space, facilitating the reconstruction of fibers connecting each pair of brain regions within this space. The whole-brain fibers will be constructed using a fiber assignment algorithm based on continuous tracking. The interregional connection density will be quantified as the fractional anisotropy (FA) value. Based on our experience, fiber tracking will cease at voxels where FA < 0.2 or when the angle between two consecutive voxel’s eigenvectors exceeds 35° (48).

### Network construction and analysis

#### Functional network

A brain network is composed of nodes and edges. We will also use the AAL template to construct the functional network to assign each brain region without the cerebellum as an anatomical region of interest (ROI). The ROIs will then be designated as nodes within the functional network, allowing us to extract the average time series for each node. An edge in a functional network is thought to be a functional connection between two brain areas. By calculating the Pearson correlation coefficient between the time series of each pair of ROI regions, we will obtain the functional connectivity matrix of each subject’s brain. It allows for a more complete understanding of the network organization since it contains additional information about the strength of functional connectivity on a continuous scale (49).

#### Structural network

The construction of structural networks based on diffusion imaging will also use AAL templates. Each brain region is referred to as a node, while detectable connections between nodes are considered edges. Two nodes are regarded as linked if at least one fiber bundle links them. For each subject, we calculate the weights of the edges using the connection density per unit of surface as its weights to obtain an undirected weighted structural connectivity network. Following that, the topological characteristics of the brain network will be assessed using graph theory. The thresholds for network groups will be quantified using a wide range of sparsity (0.05–0.5) with a 0.05 interval. To facilitate the study of the coupling between functional and structural connectivity networks, ensure structural connectivity networks are connected and have a minimum number of pseudo-edges (48).

#### Network analysis

The small-world properties, global properties, and local properties of brain networks will be analyzed using graph theory. There are five small-world properties: clustering coefficient (Cp), characteristic path length (Lp), normalized clustering coefficient (Gamma, γ), normalized characteristic path length (Lambda, λ), and small-worldness (Sigma, σ) (50, 51). A network is regarded to have small-world features when γ >> 1, λ ≈1, and σ > 1 (48, 52). Global network properties consist of global efficiency (Eg) and local efficiency (Eloc). Nodal properties, or local properties, include nodal efficiency (NE), betweenness centrality (BC), and nodal degree centrality (DC) (51, 53). A node’s NE can be measured as its capacity to transmit information to other nodes, its BC as its capacity to influence the flow of information between all other nodes, and its DC can be measured as the number of edges it connects with (52, 54).. In a previous publication, these network measures were defined in detail (54).

### Statistical analysis

Basic analyses will be conducted using SPSS 25.0 software. At baseline, independent samples t-tests will be used to determine if there is no statistical difference between the two intervention groups; paired samples t-tests will then be used to examine the differences between mean scores before and after the taVNS intervention to determine the effectiveness of the treatment. Additionally, for the imaging study, we will use two-sample t-tests to compare brain network parameters between the HC and sham groups, as well as paired-sample t-tests to determine brain network parameters between the sham and active groups. Based on age and gender as covariates, a two-sample t-test will be used to compare the small-world properties and global parameters of the anatomical network between the HC group and the sham group. The level of significance for all statistical tests is set at p< 0.05. A Bonferroni correction will be performed on the t-tests utilized to examine group differences in behavioral and brain measurements, to account for multiple comparisons.

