## Methods/design

### Study design

The study will be a randomized, double-blind, sham-controlled clinical trial, which will include patients assigned to active taVNS and sham taVNS groups and healthy subjects assigned to a healthy control group (HC). The study timeline of events is listed in **Figure 1**. For included patients, this study consisted of three basic phases: (a) a one-week baseline; (b) a consecutive 12-week treatment period without weekend interruption (Week 1 - Week 12, W1-W12); and (c) a follow-up period of 12 weeks (Week 13 – Week 24, W13 - W24). After enrollment, an interview will be used to acquire general patient information, including age, gender, duration of HFA, family history, and results of the clinical assessment tools during the baseline. Following the baseline period, patients will be assigned to one of the two treatment groups randomly to receive active taVNS or sham taVNS treatment using a random number table, which will be generated by SPSS 25.0 before enrollment of the first patient. During the follow-up period, patients will be evaluated with clinical assessment tools as well as structural and functional imaging scans.

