#### Sample size estimation

Power Analysis and Sample Size Software version 15.0 (PASS, NCSS Statistical Software, Kaysville, UT, USA) was used to determine the study’s sample size. An alpha of 0.05 and a power of 0.9 are used in the study. Based on preliminary trial results, the Clancy Autism Behavioral Scale (CABS) score indicates a curative effect, so the mean and standard deviation of the paired differences are 5 and 8, respectively (15). The PASS software calculation resulted in a minimum requirement of 34 participants per group, accounting for an estimated 20% dropout rate. Considering a 15% rate of invalid MRI data based on previous experience, a minimum of 40 subjects will be recruited per group. Therefore, 40 patients will be enrolled in each group, totaling 80 patients for the study.

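### Baseline comparability of the randomised arms is to be read from non-significant t-tests, which pass any realised gap up to about 0.445 SD, and no baseline-adjusted active-versus-sham comparison is stated

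*Protocol article*

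**What the plan says.** The Statistical analysis section of the protocol article opens with the baseline step: "independent samples t-tests will be used to determine if there is no statistical difference between the two intervention groups". The efficacy step follows: "paired samples t-tests will then be used to examine the differences between mean scores before and after the taVNS intervention". The threshold is common to all tests: "The level of significance for all statistical tests is set at p< 0.05". A correction is added: "A Bonferroni correction will be performed on the t-tests utilized to examine group differences in behavioral and brain measurements". The number of tests it covers is not given, nor whether the baseline tests are among them.

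Covariates appear once: "Based on age and gender as covariates, a two-sample t-test will be used to compare the small-world properties and global parameters". That sentence concerns healthy controls against the sham group. For active against sham, the section names a paired-sample t-test on brain network parameters and no between-arm test on the clinical scales. No baseline covariate is stated for either.

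Allocation is random (Study design): "patients will be assigned to one of the two treatment groups randomly to receive active taVNS or sham taVNS treatment using a random number table". The size is fixed under Sample size estimation: "40 patients will be enrolled in each group, totaling 80 patients for the study". Table 1 schedules five clinical measures and MRI at baseline. The section does not say what follows from a significant or a non-significant baseline test.

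**The concern.** The baseline test is asked to support a conclusion that it cannot support. Since allocation is random, the null hypothesis of no population difference is true by design, so a significant result is a chance finding. A non-significant result shows only that the realised gap lies below a limit set by the sample size. That limit has no connection with how much imbalance would matter for the outcome.

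What matters is the gap realised in these 80 children and how strongly baseline predicts follow-up. A gap that passes the check still carries into any unadjusted comparison of the arms. On change scores it acts through regression to the mean, favouring the arm that started worse. On follow-up scores it acts through persistence, favouring the arm that started better. If the arms are taken as not statistically different on the strength of p > 0.05, the reader is given a reassurance that the test does not provide, and the analysis stated next does nothing about the gap.

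**Working it through.** **Inputs from the protocol article.** 40 per arm; significance level 0.05 (two-sided assumed); random allocation; five clinical measures in Table 1. **Assumed.** Baseline-to-follow-up correlation ρ of 0.3, 0.5 or 0.7; normally distributed scores with equal SD; no treatment effect. The documents give no ρ.

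**1. The plan's own figure.** With a paired difference of mean 5 and SD 8, alpha 0.05 and power 0.90, the normal formula gives n = (8 × (1.960 + 1.282) / 5)² = 26.9, so 27. Then 27 / 0.80 = 33.75, so 34, and 34 / 0.85 = 40. The stated 34 and 40 reproduce, so 40 per arm is used below.

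**2. Largest realised gap that passes.** The test is non-significant when the observed standardised gap is below t(0.975; 78) × √(2/40) = 1.991 × 0.2236 = **0.445 SD**. If alpha were split over five scales (an assumption), the limit is t(0.995; 78) × 0.2236 = 2.640 × 0.2236 = **0.590 SD**.

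**3. How often chance produces such gaps.** A realised gap of 0.30 SD gives t = 0.30 × √20 = 1.342, p = 0.184. Randomisation alone therefore puts the gap between 0.30 and 0.445 SD in about 0.184 − 0.050 = 13% of trials for each scale. In the other direction, five independent tests at 0.05 would flag at least one scale in 1 − 0.95⁵ = 23% of correctly randomised trials. The scales overlap in content, so the true figure is probably lower.

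**4. Consequence at the edge of passing.** The observed gap is fixed at g = 0.44 SD (t = 1.968, p = 0.053). Given g and no treatment effect, the t statistics are approximately normal:
- change score: mean (1 − ρ)g / √(2(1 − ρ) × 2/40), SD √((1 + ρ)/2);
- follow-up score: mean ρg / √(2/40), SD √(1 − ρ²).

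For ρ = 0.5 both have mean 0.5 × 0.44 / 0.2236 = 0.984 and SD 0.866. The chance of exceeding 1.991 is then P(Z > (1.991 − 0.984) / 0.866) = P(Z > 1.16) ≈ 12%. Simulation with 40,000 trials per setting gives these false-positive rates:

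| ρ | Change score | Follow-up score | ANCOVA |
|---|---|---|---|
| 0.3 | 16% | 8% | 5% |
| 0.5 | 13% | 13% | 5% |
| 0.7 | 10% | 20% | 5% |

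At a gap of 0.30 SD the unadjusted rates are only about 6–7%.

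**5. Averaged over randomisations.** In 200,000 simulated null trials per ρ, both unadjusted tests reject in 5%. Among trials that pass the baseline check, the change-score test rejects in 4.0%, 4.3% and 4.6–4.7%, and the follow-up-score test in 4.7%, 4.2–4.4% and 3.6% (ρ = 0.3, 0.5, 0.7; ranges are two simulation runs).

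**6. Precision.** The variance of the arm difference is proportional to 1 − ρ² for ANCOVA (0.91, 0.75, 0.51), 2(1 − ρ) for change scores (1.40, 1.00, 0.60) and 1 for follow-up scores. ANCOVA has the smallest value at every ρ.

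**The case against.** Several counter-arguments stand, and they limit the point.

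- **Miss rate.** A reader might infer that the test would miss a half-SD imbalance about 40% of the time. That figure (40.2%) is the type II error for a true population difference of 0.5 SD, and under random allocation the population difference is zero. A realised gap of 0.5 SD at 40 per arm gives t = 0.5 × √20 = 2.24 and p = 0.028, so at 0.05 it is always flagged. It could pass only if the Bonferroni correction covered the baseline tests, which the text does not make clear.
- **No general inflation.** A reader might infer from the table that the planned check raises the trial's error rate. It does not. Averaged over trials that pass the check, the unadjusted tests reject in slightly under 5%. The 8–20% figures are conditional on a gap at the very edge of passing, and a gap that large or larger arises in only about 5% of randomisations.
- **Not the stated clinical test.** The table describes unadjusted between-arm comparisons. For the clinical scales the article states paired before/after tests, which subtract each child's own baseline. This is correct. However, a conclusion about efficacy in a sham-controlled trial needs a comparison of the arms, and subtraction does not remove regression to the mean from such a comparison.
- **Overreading.** The text speaks of no statistical difference and ties no decision to the test. It does not declare the arms equal, and it sets no gate, exclusion or choice of model.
- **Left to a statistical analysis plan.** Covariate detail may sit in a document not shown. That excuses silence, but here a method is written down: a significance test used to support comparability, followed by unadjusted tests.

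**Conclusion.** The point holds in limited form. The article uses non-significant t-tests to support the view that the randomised arms do not differ at baseline, and then states no baseline-adjusted active-versus-sham comparison. The baseline test is uninformative: realised gaps up to about 0.445 SD are taken as not statistically different, or up to about 0.59 SD if alpha were split over five scales.

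The harm is conditional, not average. It arises only if the arms are compared without adjustment and the realised gap happens to be large. In the worst case that passes, the false-positive rate is roughly two to four times nominal for the less favourable choice of score (at ρ = 0.5, 13%; at ρ = 0.7 on follow-up scores, 20%), against 5% for ANCOVA. These rates rest on assumed correlations of 0.3 to 0.7, normal scores and complete data.

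This does not invalidate the trial. It is worth changing because the better method is also the more precise one and uses data already scheduled.

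**What to change.** In the Statistical analysis section:

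1. Remove the baseline t-tests as evidence of comparability. Describe baseline values by arm as mean, SD and standardised difference, without p-values, and make no claim of balance from p > 0.05.
2. State that each clinical scale and each network parameter will be compared between active and sham with that variable's own baseline value as covariate, by ANCOVA or a repeated-measures model. Fix this in advance, whatever balance is observed.

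The cost is a change of wording and one degree of freedom per model. No visit, measurement or patient is added, because Table 1 already schedules every scale and MRI at baseline. Step 1 alone would change no efficacy estimate; step 2 is what protects the result.

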**Figure 1 f1:**
[figure not shown]
A schematic representation of the study timeline of events.

The treatment condition assignment will remain undisclosed to patients and independent observers who perform clinical assessments and MRI scan technicians until the last interview. Only the technicians performing the taVNS procedure and the physician assigning the randomization without patient contact will be aware of the group information. No communication will be allowed between patients during any phase of the study to maintain blindness.

Patients will be evaluated using the clinical assessment tools at five time points (baseline; W4, the first month of treatment; W12, right after treatment; W16, short-term follow-up; W24, long-term follow-up) (**Table 1**). MRI scan will be acquired at three time points (baseline, W12, and W24). More details regarding the clinical procedures can be found in **Figure 2**; **Table 1**. Healthy subjects in the HC group will be evaluated with the same clinical tools and undergo an MRI scan only once. The clinical endpoints are assessed by blinded observers who are not involved. Furthermore, all dropouts will be documented and reported, specifying the reasons for their withdrawal.

**Table 1 T1:** Measurements at each time point.

Measurements/time point	Recruitment	Baseline	4 weeks	12 weeks	16 weeks	24 weeks
Inclusion/exclusion criteria	√	N/A	N/A	N/A	N/A	N/A
Behavioral Checklist for Children with High-Functioning Autism/Asperger’s Disorder	N/A	√	√	√	√	√
ABC	N/A	√	√	√	√	√
CABS	N/A	√	√	√	√	√
SRS	N/A	√	√	√	√	√
WISC	N/A	√	√	√	√	√
MRI scanning	N/A	√	N/A	√	√	√

√, need to be finished; ABC, Autism Behavior Checklist; CABS, Clancy Autism Behavioral Scale; SRS, Social Responsiveness Scale; WISC, Wechsler Intelligence Scale. N/A, Not applicable.

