### Participants

#### Recruitment of participants

The Beijing Children’s Hospital Department of Psychiatry will recruit participants with HFA diagnoses from clinical practice, and a clinical multidisciplinary team involving two experienced psychiatrists will diagnose patients according to the DSM-5 diagnostic criteria. The inclusion criteria are as follows:

the age range is between 6-12 years old.Wechsler intelligence test IQ of at least 80 for Chinese children.ability and willingness to cooperate with relevant assessments and tests.right-handedness.

The exclusion criteria include:

seizure disorder or other neurological diseases (including brain tumors and craniocerebral trauma).concomitant with other mental disorders, except for attention deficit hyperactivity disorder (ADHD) and obsessive-compulsive disorder (OCD).claustrophobia.impulsivity or aggression.presence of metal products in the body.

Discontinuation and withdrawal criteria:

sudden acute illness who are unable to progress to the next phase in the study.poor adherence, and biased results will be regarded as withdrawing from the study.other uncontrollable factors or self-withdrawal from the study.

In this study, recruitment is set to occur over a period of one and a half years (from August 2023 to December 2024). Beijing primary schools will be recruited to provide healthy controls meeting the following inclusion criteria:

The age range is between 6-12 years old.IQ of at least 80.right-handedness.

Exclusion criteria include:

diagnosis of neurological or mental disorders.claustrophobia.presence of metal products in the body.

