Functional nuclear magnetic resonance imaging studies of taVNS indicate enhanced blood oxygenation level-dependent signals in the amygdala, thalamus, and frontal cortex (59). It is consistent with brain activity modulation by implantable VNS. Furthermore, stimulation of the auricular tegmentum activates the amygdala and solitary fasciculus to a greater degree (59). These nuclei and brain regions may have close associations with brain regions experiencing functional deficits in individuals with HFA. In this study, patients will undergo clinical and imaging assessments during the baseline period. Additionally, clinical evaluations will be conducted during the short-term treatment period (W4), and clinical observations and neuroimaging investigations will be carried out immediately after treatment (W12), during the early follow-up period (W16), and throughout the late follow-up period (W24). This comprehensive approach enables a thorough examination of the therapeutic effects of taVNS on patients with HFA during the early stages of treatment, as well as the establishment of relatively stable brain network changes induced by taVNS. Furthermore, follow-up observations may shed light on the long-term stability of the taVNS-induced brain network alterations. Hopefully, with the most recent advances mentioned above, it is anticipated to uncover the effectiveness of taVNS and the underlying mechanisms with structural and functional magnetic resonance imaging in our study.

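### The before/after paired t-test uses only children with both scores and ignores interim data from those who leave, so with 20% dropout planned the effect estimate is open to attrition bias of unknown size and direction

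*Protocol article*

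**What the plan says.** The Statistical analysis section of the protocol article first compares the two intervention groups at baseline. It then names the test that decides effectiveness: "paired samples t-tests will then be used to examine the differences between mean scores before and after the taVNS intervention". It does not say which scale or which later visit supplies the second score.

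Sample size estimation is built on the same quantity. For CABS, "the mean and standard deviation of the paired differences are 5 and 8, respectively", and "An alpha of 0.05 and a power of 0.9 are used in the study". The result is a "minimum requirement of 34 participants per group, accounting for an estimated 20% dropout rate". The figure then rises to 40: "Considering a 15% rate of invalid MRI data based on previous experience, a minimum of 40 subjects will be recruited per group".

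Study design and Table 1 schedule every clinical scale at baseline and at weeks 4, 12, 16 and 24. The withdrawal criteria under Recruitment of participants cover acute illness, poor adherence or biased results, and "other uncontrollable factors or self-withdrawal from the study". On children who leave, Study design says that "all dropouts will be documented and reported, specifying the reasons for their withdrawal".

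**The concern.** A paired t-test needs two numbers per child. Unless missing scores are filled in, a child who leaves before the second measurement contributes nothing to it, even if that child was assessed at week 4. Recruiting extra children replaces the lost precision. It does not make those who stay representative of those who were randomised.

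The article gives reasons to think that leaving could be related to response or to arm. Families deliver the stimulation themselves every day for 12 weeks. In the Interventions section, intensity in the active arm is set by the limit of tolerable pain, while in the sham arm it is set at a barely perceptible tingle. Stimulation may be stopped for side effects. Loss may therefore differ between arms, and any bias in the active arm need not be matched in the sham arm.

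At stake is whether the reported mean change describes all randomised children or only those who completed.

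**Working it through.** **Inputs.** Mean paired CABS change 5, SD 8, alpha 0.05 (taken as two-sided), power 0.90, dropout 20% and invalid MRI 15%, all from Sample size estimation. Visit schedule from Study design and Table 1. The difference in change between stayers and leavers is not in the article, so it is assumed below.

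**Step 1: reproduce the plan's figures.** Paired comparison, normal approximation:

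- n = ((1.960 + 1.282) × 8/5)² = 26.9, so 27 pairs.
- 27 / 0.80 = 33.75, so 34 per group.
- 34 / 0.85 = 40 per group.

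Both stated figures are recovered. The 34 is 27 complete pairs inflated for dropout, so the calculation itself counts on complete pairs.

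**Step 2: is power the problem?** With 20% lost, 40 × 0.80 = 32 pairs remain per group. Noncentral-t power of the paired test at 5/8 is 0.928 with 32 pairs (0.878 with 27). For the test as planned, power is not the issue.

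**Step 3: size of the bias.** Let d be the fraction without a pair, S the mean change of stayers and L that of leavers. The mean over all children is (1 − d)S + dL. The complete-pair test estimates S. Hence

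bias = S − [(1 − d)S + dL] = d × (S − L).

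The standard error of a group mean change with 32 pairs is 8/√32 = 1.41.

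| Assumed gap S − L (CABS points) | Bias if all 20% leave before week 12 | As a share of the planned 5 | In standard errors (1.41) | Bias if half of them leave before week 12 (d = 0.10) |
|---|---|---|---|---|
| 0 | 0 | 0% | 0 | 0 |
| 2 | 0.4 | 8% | 0.28 | 0.2 |
| 5 | 1.0 | 20% | 0.71 | 0.5 |
| 8 | 1.6 | 32% | 1.13 | 0.8 |

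A negative gap gives the same sizes with the opposite sign. For active versus sham, the bias is d × (S − L) in the active arm minus the same product in the sham arm. It cancels only if the two products are equal.

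**Step 4: which children are affected.** Taking week 12 as the second measurement:

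| Time of leaving | Baseline–week 12 pair? | Interim score that the paired test leaves unused? |
|---|---|---|
| Before week 4 | No | None exists |
| Between week 4 and week 12 | No | Yes, week 4 |
| After week 12 | Yes | Not relevant to the week 12 test |

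All losses before week 12 can bias the week 12 estimate. Only the middle row leaves usable data aside. If week 24 is the second measurement, children lost between weeks 12 and 24 also join the affected group, with scores at week 4, week 12 and possibly week 16 unused.

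**The case against.** The strongest reply is that this is a condensed article. Analysis sets and imputation rules commonly sit in a full protocol or analysis plan that is not shown, and a paired t-test can be run on imputed data. This stands in part: the absence of an imputation rule is no finding, and the article nowhere says that dropouts are excluded or that interim scores are thrown away. It does not remove the point, which concerns the method the article does name. That method takes one before and one after score per child.

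A reader might infer four stronger things, and the document supports none of them.

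- *That the whole 20%, or 8 of 40 per arm, would have no usable score.* The rate has no time point and is not split by cause. Follow-up runs to week 24, and children lost after week 12 still have a week 12 pair.
- *That completers overstate the effect.* Families who see no benefit may leave, but so may children who have improved, or who respond but find the stimulation uncomfortable. The sign is open.
- *That the overstatement can be put at some 6–20%.* Such figures (completer means of about 5.3 to 6.0 against a true 5.0) need an assumed week 4 mean change of 2.5, a week 4–week 12 correlation of 0.5 to 0.7, and dropout odds raised 1.5 to 3 fold per SD of poorer week 4 response, with all loss after week 4. None of these is in the article. Because dropout in that set-up depends only on an observed score, a likelihood model recovers the truth by construction, so the exercise is no evidence for the model.
- *That the Discussion promises a long-term clinical comparison.* The sentence that "follow-up observations may shed light on the long-term stability of the taVNS-induced brain network alterations" concerns imaging, not the clinical scales.

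It is also fair to say that a mixed model is not the only remedy (multiple imputation before a paired test is another), and that a between-arm contrast changes more than the handling of dropout.

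**Conclusion.** The point holds in a limited form. The named effectiveness test is a complete-pair analysis unless missing scores are filled in, and it makes no use of interim scores from children who leave before the second measurement. The article itself plans for 20% dropout and allows for it only through numbers.

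The estimate is therefore open to attrition bias whose size and direction the document does not fix. The 0.4 to 1.6 point range rests on two assumptions: gaps of 2 to 8 points, and all dropout falling before the second measurement. The sample size arithmetic is not in dispute. The change is worth making because the interim data are already scheduled and the cost is small.

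**What to change.** In Statistical analysis, replace the paired t-tests on the clinical scales with one repeated-measures mixed model per scale:

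- all randomised children with any post-baseline score;
- baseline score as covariate;
- arm, visit (weeks 4, 12, 16 and 24) and arm-by-visit terms;
- active-versus-sham differences at weeks 12 and 24 read from that one model, with within-arm changes reported from it if wanted.

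Add one sensitivity analysis that departs from missing-at-random, for example imputing active-arm dropouts from the sham arm's course. This is a separate imputation step beyond the mixed-model procedure. It explores the assumption and does not test it. Report numbers lost by arm and visit. Children lost before week 4 add no outcome data to the main model and should be counted explicitly.

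**Cost.** Changed analysis wording and somewhat more analysis work, with no new visits, data or patients. The model relies on missing-at-random. The sample size was derived for a within-group paired change, so its 0.9 power does not carry over to the between-arm contrast. If 5 and 8 were the between-arm difference and the SD of change, a plain two-sample t-test with 32 per arm would have power 0.692, before any gain from baseline adjustment or the extra visits. That is a separate matter, but it should be stated when the wording changes.
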